### Randomisation

Participants will be remotely randomised, following consent, using an online computerised randomisation system created by the Centre for Trials Research at Cardiff University. This will be operational 24 h a day. In addition, an 8.30 a.m. to 6.30 p.m. telephone back up will be available if the online system fails or the general practice has problems accessing the online site.

Participants will be randomised in a 1:1 ratio to receive either usual care alone (control) or usual care with the addition of CRP POCT (intervention). Randomisation will use minimisation, with a random element set at 80% to improve the integrity of the randomisation process. Anthonisen criteria (categorised as type 1, 2 or 3) will be used as a minimisation variable, so that balance is achieved with respect to differing levels of COPD exacerbation severity. Remote allocation will maintain allocation concealment from both the participant and the recruiting clinician up to the point of intervention, as this is an open study.

### Data collection

In order to facilitate the process of patient recruitment and data collection into busy routine clinics, data collection can be conducted by any suitably trained clinician (nurse, health care assistant or GP). The timing and type of assessment (Standard Protocol Items: Recommendations for Interventional Trials (SPIRIT) Figure) is described in Fig. 2.

**Fig. 2 Fig2:**
[figure not shown]
Schedule of assessments (SPIRIT figure)

A SPIRIT Checklist is included as an Additional file (Additional file 1).

### Baseline appointment

The clinician carrying out the baseline appointment will record the number of days that the participant reports having symptoms from the acute exacerbation, their medical history, and clinical examination results (temperature, pulse, oxygen saturation and whether tachypnoea, crackles, wheezes, diminished vesicular sounds and evidence of consolidation).

A sputum sample (when participants are able to produce sputum) and throat swab samples (using charcoal swabs) will be obtained from the patient at the baseline appointment and recorded on the baseline Case Report Form (CRF). Recruiting clinicians will assess and record, on the baseline CRF, the colour of the participant’s sputum against a Bronkotest chart (Bronkotest Ltd.).

Participants will be asked to self-complete the baseline CCQ and the baseline European Quality of Life-5 dimensions (EQ-5D) questionnaire at this visit. The CRP test results will be recorded on the baseline CRF for those randomised to care with the addition of the CRP POCT.

Antibiotic prescribing and other management decisions will be recorded for all patients following randomisation, and after CRP testing for those randomised to the intervention.

### Follow-up data collection

The trial team will aim to telephone all participants at 1 week and 2 weeks post randomisation to collect information on their medication usage during that time period and also to obtain their responses to questions on the week-1 and week-2 CCQ and EQ-5D questionnaires. Participants will be invited to return to the surgery for a face-to-face consultation at 4 weeks post randomisation. The Chronic Respiratory Disease Questionnaire, self-administered, standardised (CRQ-SAS) and the EQ-5D will be posted to participants for completion and return at 6 months.

*Telephone calls*
**–**
*week 1* (time window of −1/+2 working days) and *week 2* (time window of −1/+7 working days).

Participants will be contacted by telephone by a member of the trial team. Participants will be given paper versions of the week-1 and-week 2 CCQ and EQ-5D questionnaires at their baseline visit and asked to complete them on each appropriate day (day 8 and day 15, with the baseline appointment being on day 1) prior to the telephone interview in order to facilitate data collection.

*Face-to-face visit*
**–**
*week 4* (time window of −3/+14 working days).

The week-4 face-to-face appointment will be arranged at the time of baseline assessment and appointments will be conducted by a member of the clinical team in the general practice or a clinical study officer/research nurse working for the local clinical research network at the general practice. The following data will be captured: medication consumption, adverse effects, time off paid work, diagnosis of pneumonia since the baseline appointment, any further CRP tests since the baseline appointment, health care consultations. Sputum (where possible) and throat swab samples will be obtained from the participant and the colour of the sputum assessed against a Bronkotest chart. Participants will be asked to self-complete the week-4 CCQ and the week-4 EQ-5D questionnaire at this visit. If a successful appointment does not take place at week 4, the study team will contact the participant by telephone to obtain a minimum dataset. This dataset includes antibiotic consumption during the third and fourth weeks after randomisation, health care resource use and completion of the CCQ and EQ-5D questionnaires. If the participant has missed their week-1 or week-2 follow-up telephone call, the site will be asked to carry out a minimum dataset with the participant at the week-4 appointment. This dataset captures information on the participants’ medication consumption.

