## Methods/design

### Objectives

The primary objective is to determine whether the addition of a CRP POCT (with training on test use and advice on interpretation) to usual care for managing AECOPD leads to a reduction in antibiotic consumption for AECOPD without negatively impacting on COPD health status, compared with usual care alone. Table 1 lists the primary and secondary objectives and outcome measures.

**Table 1 Tab1:** Primary and secondary objectives and outcome measures

	Objectives	Outcome measures	Time point(s) of evaluation of this outcome measure
Primary	To determine whether the addition of a CRP POCT (with training on test use and advice on interpretation) to usual care for managing AECOPD leads to a reduction in antibiotic consumption for AECOPD compared to usual care alone	Antibiotic consumption (any consumption of antibiotics for AECOPD vs. no consumption of antibiotics for AECOPD)	First 4 weeks post randomisation
Primary	To determine whether the addition of a CRP POCT (with training on test use and advice on interpretation) to usual care for managing AECOPD leads to a reduction in antibiotic consumption for AECOPD without negatively impacting on COPD health status compared to usual care alone	Recovery in terms of COPD health status as assessed using the Clinical COPD Questionnaire (CCQ) total scores	2 weeks post randomisation
Secondary	To assess the effect of using a CRP POCT for AECOPD in primary care on:	Prevalence of potentially pathogenic bacteria (including *S. pneumoniae*, *Haemophilus* spp. and *Enterobacteriacae*) cultured from sputum at 4 weeks and the proportion of bacteria that are resistant	4 weeks post-randomisation
		Prevalence of commensal organisms cultured from throat swabs at 4 weeks and proportion of bacteria that are resistant	4 weeks post randomisation
		COPD health status over time measured using the CCQ total score	At weeks 1, 2 and 4 post randomisation
		CCQ symptoms domain	At weeks 1, 2 and 4 post randomisation
		CCQ function state domain	At weeks 1, 2 and 4 post randomisation
		CCQ mental state domain	At weeks 1, 2 and 4 post randomisation
		Total antibiotic consumption (number of days antibiotics consumed for AECOPD/any reason)	First 4 weeks post randomisation
		Health utility measured using the EuroQol-5D (EQ-5D)	At weeks 1, 2 and 4 and at month 6 post randomisation
		All-cause antibiotic consumption	During the first 4 weeks post randomisation
		Antibiotic prescribing	At the index consultation

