### Outcome measures

The co-primary outcome measure will comprise:Antibiotic consumption at any point during the 4 weeks post randomisation for AECOPD, measured using telephone interviews at 1 week and 2 weeks and face-to-face interview at 4 weeksCOPD health status measured by the Clinical COPD Questionnaire (CCQ)[35] via telephone interview at 2 weeks. The CCQ is a patient-centred health status measure that has been well validated and is widely used in patients with COPD [36]

A 4-week time window was selected for the antibiotic consumption outcome in order to measure the consumption of antibiotics prescribed at the initial consultation in addition to those that are related to the AECOPD in question, but are initiated or prescribed at a later date. The CCQ outcome is measured at 2 weeks as this is the time when most patients will have recovered and, therefore, the point at which a difference would be most indicative of a delayed recovery.

Secondary outcome measures are listed in Table 1.

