### Adverse events

Hospitalisation is expected within this patient population and will be collected and reported as part of routine follow-up. All other events fulfilling the definition of a serious adverse event (SAE), including death, that occur between the time of consent and the 4-week follow-up will be reported to the coordinating research centre within 24 h of the site becoming aware of the event.

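### The week-4 visit may fall 3 working days early, leaving about 3–5 days of the 4-week antibiotic-consumption period without an interview; a late visit can add later events to the week-4 pneumonia count

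*Protocol article*

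**What the plan says.** Table 1 of the protocol article (Objectives) defines the first co-primary as "Antibiotic consumption (any consumption of antibiotics for AECOPD vs. no consumption of antibiotics for AECOPD"), with the evaluation period "First 4 weeks post randomisation". Outcome measures describes it as "Antibiotic consumption at any point during the 4 weeks post randomisation for AECOPD, measured using telephone interviews at 1 week and 2 weeks" and by face-to-face interview at 4 weeks. The same section explains that 4 weeks was chosen so that antibiotics begun after the index consultation, but related to the same exacerbation, would also be counted.

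Follow-up data collection numbers the days: questionnaires are due on "day 8 and day 15, with the baseline appointment being on day 1". The week-2 call has a "time window of −1/+7 working days" and the week-4 visit a "time window of −3/+14 working days". Items captured at that visit include medication consumption and adverse effects, with no recall period stated, and "diagnosis of pneumonia since the baseline appointment, any further CRP tests since the baseline appointment, health care consultations". If no week-4 appointment succeeds, a telephone call collects a minimum dataset that covers antibiotic use in weeks 3 and 4.

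Table 1 lists incidence of pneumonia, by patient and GP report, at week 4 and month 6. The 6-month records review collects prescriptions. Adverse events sets the reporting period for serious adverse events (SAEs) other than hospitalisation: those "that occur between the time of consent and the 4-week follow-up will be reported to the coordinating research centre within 24 h".

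**The concern.** An outcome defined over a fixed 4 weeks needs its last interview at or after the end of those 4 weeks. Here the last interview may lawfully come before it. A participant with no antibiotics so far who starts a course after an early visit would be classed as a non-consumer, although the period was lengthened to 4 weeks precisely to include late starts. In a trial where the CRP test may lead to antibiotics being withheld at first, those late starts are part of what the outcome has to measure.

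The opposite problem affects pneumonia. It is counted from baseline to whenever the visit happens, yet reported as a week-4 outcome. It is a safety-relevant secondary measure, and its observation period would differ between participants.

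**Working it through.** **Step 1: the window in calendar days.** Inputs: baseline is day 1; weeks 1 and 2 are days 8 and 15, so by the same numbering week 4 is day 29; the window is −3/+14 working days. Counting Monday to Friday and ignoring public holidays (which would widen it):

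| Baseline weekday | Earliest week-4 visit | Latest week-4 visit | Latest week-2 call |
|---|---|---|---|
| Monday | day 24 | day 47 | day 24 |
| Tuesday | day 24 | day 49 | day 24 |
| Wednesday | day 24 | day 49 | day 24 |
| Thursday | day 26 | day 49 | day 26 |
| Friday | day 26 | day 49 | day 26 |

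**Step 2: days not covered by interview.** If the 4 weeks end on day 28, a day-24 visit leaves days 24–28 wholly or partly unasked (up to 5 days; 5/28 = 18% of the period), and a day-26 visit leaves days 26–28 (up to 3). If they end on day 29, the unasked whole days are 25–29 (5) and 27–29 (3). So about 3–5 days at the edge of the window, and fewer for visits nearer day 29.

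**Step 3: does anything else described close the gap?**
- The week-2 call, even at its latest, comes no later than the earliest permitted week-4 visit for the same baseline weekday (table above).
- The telephone fallback applies only when the week-4 appointment has not succeeded. A day-24 visit has succeeded.
- The records review covers prescriptions, but the outcome is consumption. Participant recruitment and consent acknowledges that some patients hold antibiotics at home in rescue packs; a course started from a pack on days 25–28 need not appear as a prescription then.

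**Step 4: pneumonia.** With recall from baseline, the observation period runs from 24 to 49 days depending on the visit date (49/24 = 2.04). A visit on day 47–49 lies 19–21 days beyond day 28.

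**Step 5: possible effect on the co-primary.** First, the plan's own figure. With p1 = 0.70, p2 = 0.55, two-sided 5%, 90% power and pooled variance under the null:

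n per arm = [1.960 × √(2 × 0.625 × 0.375) + 1.282 × √(0.70 × 0.30 + 0.55 × 0.45)]² / 0.15² = (1.342 + 0.867)² / 0.0225 = 216.8, so 217 per arm and 434 in total, as stated.

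With 650 recruited and 20% lost, 650 × 0.8 = 520, or 260 per arm. The same formula gives power 0.9443. The documents give no rate of late first courses, so the following are assumptions:

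| Assumed under-capture, both arms | Proportions compared | Power |
|---|---|---|
| none | 0.70 vs 0.55 | 0.9443 |
| 1 percentage point | 0.69 vs 0.54 | 0.9422 |
| 3 percentage points | 0.67 vs 0.52 | 0.9385 |
| 5% of consumers | 0.665 vs 0.5225 | 0.9135 |

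The last row is demanding: 0.05 × 0.70 = 3.5% of usual-care participants and 0.05 × 0.55 = 2.75% of CRP participants would each have to be seen early and then take their first antibiotic in the few remaining days.

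**The case against.** The case for leaving the window alone has real force. The outcome is any versus none, so only a participant with no antibiotic so far who first takes one in the last few days is misclassified. The window is the same in both arms, and few visits may fall at its early edge. The 18% is a share of days, not a bias. Prescriptions over 6 months would reveal a late-prescribed course, so the tail is not wholly unseen. The case report form may carry recall limits and event dates that a journal article does not print. All this stands as to size. It does not remove the truncation, because the early allowance is itself stated in the article and no described contact follows it.

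Three stronger readings are tempting, and the documents support none of them.

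- A reader might infer that antibiotic consumption overruns in late attenders. The since-baseline wording is attached only to pneumonia and further CRP tests; the outcome is fixed at 4 weeks; and the one recall period stated for late antibiotic data, in the fallback call, is limited to weeks 3 and 4. A late visit means longer recall, not a longer outcome period. Further CRP tests are not an outcome in Table 1.
- A reader might infer bias between arms, with relapsing patients seen at different times. The appointment is arranged at baseline, before recovery or relapse is known. Rescheduling could happen, but nothing shows that it would differ by arm.
- A reader might infer that the SAE period should be cut at day 28. It is a reporting rule, not a Table 1 outcome, and shortening it would drop reports now required.

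**Conclusion.** The point holds in a limited form. An in-window early visit ends interview follow-up about 3–5 days before the 4-week antibiotic period ends, and no described contact completes it. Separately, pneumonia up to about 3 weeks after week 4 can enter the week-4 secondary outcome; the month-6 assessment is not touched by this.

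The effect on the co-primary comparison is probably small: under the assumed losses above, power stays above 91% for that outcome. This rests on week 4 being day 29, on no public holidays, on 520 evaluable participants, and on under-capture of similar proportion in both arms. The share of visits held early is not given. This is a worthwhile low-cost improvement to measurement, not a threat to the trial's main conclusion.

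**What to change.** 1. Set the week-4 window to 0/+14 working days, so that the appointment is booked on or after day 29. If a visit does fall earlier, make a short call on or after day 29 about antibiotic use in the remaining days.
2. At the face-to-face visit, limit the medication questions to the end of week 4, as the fallback call already does, and keep the existing catch-up for missed week-1 or week-2 calls.
3. Record the date of any pneumonia diagnosis, and count in the week-4 outcome only those within 4 weeks of randomisation.
4. Leave the SAE reporting period as it is. If SAEs are compared between arms, count them over one fixed period common to all participants.

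The cost is a change to protocol and form wording, slightly less scheduling freedom for practices, and an occasional short call. No extra participants or visits are needed.

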### Collection of relevant data from electronic medical records at 6 months

Antibiotics prescribed in the 12 months prior to study inclusion, spirometry results and a full blood count result obtained prior to study inclusion will be recorded.

Spirometry results, prescriptions, and health service utilisation data will be recorded for each participant for the 6-month period following randomisation. General practices will be asked to provide these data on a proforma basis from a medical records review; alternatively, the data will be collected by a member of the trial team or clinical study officer/research nurse.

### Patient self-reported CRQ-SAS and EQ-5D – 6 months

Participants will be sent a copy of the CRQ-SAS and EQ-5D at 6 months post randomisation by post. Participants will be telephoned by the trial team 1 week after the due date to remind them to return the questionnaire by post or to offer to complete these instruments over the telephone at that point. If the questionnaire is not received within 1 week of the first telephone reminder, the trial team will telephone the participant again.

### Adverse events

Hospitalisation is expected within this patient population and will be collected and reported as part of routine follow-up. All other events fulfilling the definition of a serious adverse event (SAE), including death, that occur between the time of consent and the 4-week follow-up will be reported to the coordinating research centre within 24 h of the site becoming aware of the event.

### Microbiological assessment

Sputum (if available) and throat swab samples will be obtained at the recruitment visit (baseline) and at the face-to-face visit at week 4 and will be sent to the Specialist Antimicrobial Chemotherapy Unit (SACU), Public Health Wales at the University Hospital of Wales. Not all patients will be able to produce a sputum sample on request and, therefore, we would expect to have a lower return rate for these samples as compared to the throat swab samples at both baseline and week 4.

Sputum sample appearance (including colour and consistency) will be noted and all samples will be processed using the laboratory’s standard operating procedures. Potential pathogenic bacteria (including *S. pneumoniae*, *Haemophilus influenzae/parainfluenzae*, *Pseudomonas* spp., *Enterobacteriaceae* and *Staphylococcus aureus*) found in the sputum will be identified using the Matrix Assisted Laser Desorption Ionising Time of Flight Mass Spectrometry (MALDI-ToF-MS) and semiquantitative counts recorded. Susceptibilities will be performed on relevant bacterial species from sputum samples by disc diffusion using European Committee on Antimicrobial Susceptibility Testing (EUCAST) methodology and breakpoints. Throat swabs (charcoal) will be added to Tryptone soya broth and 50 μL spiral plated onto a range of non-selective plates and selective plates for identification purposes (e.g. Columbia blood agar, Isosensitest with blood) and antimicrobial-selective plates containing penicillin, third-generation cephalosporins, doxycycline, levofloxacin and clarithromycin at concentrations consistent with EUCAST breakpoints). Total bacterial counts of commensal organisms will be recorded on non-selective and selective agars; proportional quantification of resistant isolates will be determined from the selective media. All pathogens recovered, sputum samples and remaining broth from throat swabs will be stored at −80 °C.

### Process evaluation

A qualitative process evaluation will be embedded in the trial to provide a better understanding of the implementation and receipt of the intervention and the context in which it is delivered. This will aid interpretation of outcome results and possible uptake of the intervention should the trial have favourable benefits and risks [37]. Semistructured interviews will be carried out with up to 30 members of the participating primary care teams and up to 30 patients to gather in-depth information on their experience of participating in the study and their thoughts of management of AECOPD in primary care. These will be conducted by telephone. Approximately a third of these interviews will take place during the pilot phase of the trial, with the remainder being carried out during the full trial.

The objectives of the qualitative process evaluation are to:Understand patient perspectives on the use of the CRP POCT to help guide the management of AECOPDUnderstand clinician perspectives on the use of the CRP POCT to help guide the management of AECOPDUnderstand barriers and facilitators to using the CRP POCT in primary care and to inform possible implementation and roll-out (if appropriate), including:Views of primary care team members on conducting POCT testing for AECOPD in primary carePatient perspectives on the routine management of AECOPD, including the use of antibioticsPrimary care clinicians’ views on the challenges involved in the routine management of AECOPD

An additional objective during the pilot phase will be to examine perceptions of the research processes to identify facilitators and barriers to participation so that these can be addressed as far as possible prior to the full trial phase.

Flexible topic guides will be used for the clinician and patient interviews covering themes relating to these objectives. The interviews will be audio-recorded and will be approximately 30 min in duration.

Patients who have agreed to be contacted for an interview will be telephoned by the research team within 2 weeks of their 4-week follow-up appointment with their GP (i.e. 4–6 weeks from their initial consultation). The trial team will write to participating practices to invite them to take part in the qualitative interviews, and this will be followed up by a telephone call to arrange an interview with a member of the primary care team.

Purposive sampling will be used to capture a range of views from health professionals and patients. During the internal pilot stage, approximately equal numbers of patients in each trial arm will be sampled to assess the acceptability of research procedures in each group. In the full trial, only patients from the CRP POCT arm will be interviewed. Patients will be sampled across geographical regions and will include patients who had, or had not, been prescribed antibiotics at their initial consultation. Similarly, general practices across all regions will be sampled. Interviews will be conducted with prescribing clinicians (i.e. GPs and nurse practitioners) and non-prescribing members of the primary care team who have been involved with the trial. In the internal pilot phase of the trial, recruitment of the primary care team will be associated with experience of the research processes (e.g. recruitment of patients), while in the full trial phase we will focus on members of the primary care team with experience of carrying out and/or interpreting results of the CRP POCT.

As part of a quantitative process evaluation, we will estimate adherence to the allocated treatment arm based on patient reports of receiving a finger-prick blood test and, where possible, verify and supplement these data from other sources, such as GP records and CSV files stored on the CRP Afinion machine.

